### Ethical approval

Ethical approval for the trial was received from the National Ethics Committee for Human Research (ref: 14 073) and the National Drug Agency (141299B-21). The regional governmental health agency also approved the various locations for the intervention (DOS-01115-0577-D).

### Intervention

The PAPA group will participate in two supervised sessions per week for the first 2.5 months and only one supervised session per week for the last 2.5 months. For the first 2.5 months, these patients will be advised to carry out at least one more session during the week on their own to meet the American College of Sports Medicine (ACSM) guidelines for cardiac patients [28]. However, they will be encouraged to carry out two autonomous sessions per week for the last 2.5 months. The supervised sessions will always be held at the same time of day and on the same day of the week with the same instructor. These sessions will include one session of Nordic walking (45 min to 1 h) at low to moderate intensity and one session of circuit training (1 h) at moderate to high intensity. The intensity levels will be defined in accordance with ACSM guidelines [28]. The session contents will be individualized according to each patient’s heart rate using a heart rate monitor (Polar FT1 heart-rate monitor watch). After controlling the resting heart rate and maximal heart rate, training windows will be calculated for each participant and used during the PA sessions. This will allow them to work at different intensities. The instructor will be trained to deliver an autonomy-supportive coaching style [41] as autonomous motivation has been shown to strengthen habit formation [19]. The tools we will use and the strategies we will implement are all aimed at supporting exercise instigation in terms of planning and preparatory behaviors (Barz et al. [4]). The goal is to develop autonomy, self-confidence and knowledge so that the participants can exercise by themselves in their homes. An individualized exercise prescription based on heart rate and current exercise capacity will be a core component of the intervention. Autonomous practice will be promoted in this group with support to aid habit formation. First, they will receive a pamphlet on PA (i.e., tips on safety rules, health benefits, nutrition, stretching, how to use a heart rate monitor, how to breathe) and a PA program containing a list of Nordic walking and cardio-training activities that can be done in their home environment. They will also receive the calendar used by Gardner et al. [20] that can be used as a tool for forming new habits. The calendar is generic and patients will be invited to use it in planning when and where they will do their PA sessions; they will thus be expected to write session plans down on the calendar. They will be advised to put the calendar in a place where they will see it every day (e.g., on the fridge and/or a bathroom mirror) so that they will have frequent reminders of their PA session. They will then be called every 2 weeks for an approximately15-min conversation with a researcher trained in habit formation theory. This researcher will help the patients to choose an appropriate moment and an appropriate context for the autonomous PA sessions and remind them to stick with their plans.

The SPA group will have two supervised sessions over 5 months. They will also be advised to carry out at least one more session on their own during the week to meet with the American College of Sports Medicine (ACSM) guidelines for cardiac patients [28] (Fig. 1).

**Fig. 1 Fig1:**
[figure not shown]
Illustration of the intervention showing the number of supervised sessions and autonomous sessions in the progressively autonomous (PAPA) group and the supervised (SPA) group

### Outcome measures

#### Demographics

Demographic (gender, birthdate, zip code) and medical (cardiovascular disease or cardiac deficiency) data will be collected at baseline.

#### Behavioral measures

PA behavior will be assessed using a self-report questionnaire extensively used in the literature, the International Physical Activity Questionnaire (IPAQ) [14] at time (T) 0, T5, T7, T9 and T12 months. The questionnaire responses will be computed as energy requirements defined as METs (multiples of the resting metabolic rate). Based on previous research in other chronic diseases (e.g., [31, 32]), a subsample using a GT3X+ accelerometer will comprise 30 % of the participants selected randomly from among volunteers. According to this meta-analysis, an acceptable level of agreement between IPAQ and GT3X+ indicated a small to moderate association (r = .29). They will wear the GT3X for one week (score in METs) at T0, T5 and T12 in order to check whether the self-reported PA measure correlates with the objective PA measure in the context of our study. The PA adherence will be assessed by reporting on the participation in the two supervised sessions per week and the autonomous session.

#### Physical measures

The New York Heart Association (NYHA) test will be measured at T0 and T12 by the cardiologist to assess cardiovascular health [6]. Patients with heart failure will answer four questions in relation to how they feel during rest or physical activity. They will then be placed in one of four categories based on how limited they are during physical activity; the limitations/symptoms regard normal breathing and the varying degrees in shortness of breath and/or angina pain. General physical condition will be measured at T0, T5 and T12 with the 6-min walking test [30], a handgrip strength test [37] and the sit to stand test [7].

#### Psychological measures

All psychological measures will be made at T0, T5 and T12 months. The strength of PA habits will be measured using the Self-Report Behavioral Automaticity Index (SRBAI) [20]. We used a French adaptation of these items that was validated by Boiché [8]. The SRBAI is a four-item questionnaire (“I do automatically”; “I do without thinking”; “I do without having to consciously remember”; and “I start doing before I realize”) that is typically used by calculating the average automaticity score. Self-determined motivation will be assessed using the sport motivation scale [10] to rate each participant’s motivation regarding PA behavior. We will score the scale’s seven types of motivation according to self-determination theory: (a) amotivation; extrinsic motivation with (b) external regulation, (c) introjected regulation, (d) identified regulation, (e) integrated regulation and (f) intrinsic regulation (Deci & Ryan [17]). Last, we will assess the eventual changes in quality of life using the SF-36 questionnaire [44], which measures life quality in the domains of physical functioning, role-physical, bodily pain, general health, vitality, social functioning, role-emotional and mental health.

#### Economic measures

The quality-adjusted life-year (QALY) will be calculated at T0, T5 and T12 in order to assess the predicted increase in life expectancy. This widely used indicator is a measure based on the preferences expressed by the patients themselves with respect to different health states. This assessment allows for the adjustment in life years gained by the quality of life rated on a five-dimension scale, the “EQ5D” [13]. Participants in the experiment will be compared with a control group composed of the 78 individuals who initially volunteered to participate in the study but then realized they could not do so for several reasons: they were unavailable for the entire study, had changed their minds or had problems commuting to the PA sessions. To improve the reliability of the QALY, we will also include data on the number and duration of hospitalizations during the protocol and health care consumption; this information will be provided by the reimbursement databases for the year preceding inclusion and at 5 months of intervention and 6 months of follow-up.

We will also assess program cost by financially assessing the time spent by the various stakeholders, the travel cost for patients, and the cost of materials and fitness center rental space.

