#### Secondary research objectives

Exploratory analyses will assess the differences between the two groups in motivation for PA, automaticity of PA behavior and quality of life. We will also compare the evolution in the patients’ physical condition. Last, we will evaluate the cost-effectiveness of the two interventions. We hypothesize that the PAPA program promoting habit formation will result in better physical condition, motivation, automaticity of PA behavior and quality of life at the end of follow-up compared with the SPA program. We also hypothesize that the PAPA program will cost less than the SPA program.

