### Sample size

The sample size was calculated using the simulation method of PASS 14 software (NCSS, Kaysville, USA) for power analysis with a mixed model. An alpha risk of 5 % and a bilateral hypothesis were taken into account for the power analysis. We estimated the expected scores of the participants in each arm of our study on the basis of the results of large-scale studies [34, 35, 38] that assessed PA behavior maintenance after CR with a questionnaire providing an average score of PA minutes per week. Given the linear effect of time, the change in PA behaviors after SPA suggested that the weekly time spent in PA behavior would be reduced by 5 min very month following the intervention. This result was used to infer the PA level of the group at each measurement point post-program. Several studies have shown that interventions designed to promote maintenance can lead to stabilized or even slightly increased PA behaviors over time (e.g., [2, 29, 34, 38]). We therefore predicted no change in the amount of PA behavior for the PAPA group after the intervention. The power analysis used a similar average score immediately after the intervention of 200 min/week for both groups, a general between-subject variability of 90 min/week, and an autocorrelation of the repeated measures of .55. ([name], [name], [name]. (unpublished manuscript). Testing the effect of text messaging cues to promote physical activity habits: A worksite-based exploratory intervention). The results after 1000 simulations indicated that 50 evaluable participants (25 participants in each arm) would be required to find the time-by-condition interaction effect with an 80 % power level. Assuming about 10 % of patients mistakenly included, lost to follow-up or withdrawing from the study, we randomized 56 participants (28 participants in each of the two arms).

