### Participants

#### Recruitment strategy

The study is being conducted in the Alpes-Maritimes region of southern France; it began in 2014 and will run until 2016. CVD patients are identified from the electronic records of a public health insurance company for independent workers. The insurance company initially contacts the patients (*N* = 2248) by email, providing a detailed description of the project including the research objectives, subject requirements, timetable and the testing and training facilities. Potential participants are invited to contact the insurance company if they are interested in the experiment. Phone screening was conducted with 91 volunteers in October 2014. Then, they will have a free medical checkup with the study cardiologist, including a maximal effort test and an electrocardiogram.

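### The only QALY comparison specified is non-randomised and does not answer the PAPA-versus-SPA economic objective; the care-use window stops a month short of T12, and the 78 controls are not accounted for.

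*Protocol article*

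**What the plan says.** Under Secondary research objectives the economic aim is given as "we will evaluate the cost-effectiveness of the two interventions", together with the hypothesis that PAPA will be the cheaper programme.

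Under Economic measures, EQ-5D-based QALYs are planned at T0, T5 and T12. The comparison attached to them is "Participants in the experiment will be compared with a control group composed of the 78 individuals who initially volunteered to participate in the study". The reasons these people did not take part are listed as "they were unavailable for the entire study, had changed their minds or had problems commuting to the PA sessions".

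The same section adds care-use data: "To improve the reliability of the QALY, we will also include data on the number and duration of hospitalizations". The care-use data come from reimbursement databases "for the year preceding inclusion and at 5 months of intervention and 6 months of follow-up". Programme cost is a separate paragraph, covering staff time, patient travel, materials and rental of space.

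On numbers, Recruitment strategy says "The insurance company initially contacts the patients (*N* = 2248) by email" and then "Phone screening was conducted with 91 volunteers in October 2014". Sample size gives 56 randomised, 28 per arm.

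Statistics and data analysis gives one model for the secondary objectives: a general linear model with time, experimental condition and their interaction.

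**The concern.** The objective asks which of two randomised programmes is better value. Randomisation answers that without selection bias. The QALY comparison that the article spells out instead sets trial participants, arms undivided, against people who selected themselves out. Being free to attend, staying willing and being able to travel may all relate to health and to use of care. Travel is also one of the article's own programme cost items. A difference between participants and these 78 could therefore reflect who they are rather than what the programmes did.

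Three further features weaken the economic section. Care use and QALYs are not collected over the same period. The number 78 cannot be traced from the recruitment figures. And care use, which is resource consumption, is described as something that makes the QALY more reliable.

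At stake is the secondary conclusion on value for money, which the article's Discussion links to possible savings in the cost of rehabilitation.

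**Working it through.** **1. Does the stated comparison answer the objective?** Let P, S and C be the mean QALYs of PAPA, SPA and the 78. The objective needs P − S.

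- Pooled participants against the 78, with equal arms of 28, gives (P + S)/2 − C. If P rises and S falls by the same amount d, this becomes (P + d + S − d)/2 − C, which is unchanged. The pooled contrast carries no information on P − S.
- Each arm against the 78 gives P − C and S − C. Their difference is (P − C) − (S − C) = P − S. The 78 cancel, so they add nothing to the between-arm question.
- If the 78 differ from the trial population by a selection bias b, then P − C, S − C and the pooled contrast are all shifted by b, while P − S is not. The article gives nothing from which b could be estimated.

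**2. Do the counts reconcile?** Inputs: 91 phone-screened (Recruitment strategy); 56 randomised (Sample size); 78 controls (Economic measures).

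- The 56 itself reproduces: 50 evaluable / (1 − 0.10) = 55.6, rounded up to 56; per arm 25 / 0.90 = 27.8, rounded up to 28.
- Screened but not randomised: 91 − 56 = 35 at most. Anyone excluded at the cardiologist's checkup lowers the number available as willing-but-unable controls.
- Needed for 78 controls and 56 randomised: 78 + 56 = 134, which exceeds 91 by 43.
- If all 78 came from the 91: 91 − 78 = 13, too few to randomise 56.

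Taking the 56 as drawn from the 91, at least 78 − 35 = 43 of the controls were outside that screening. Everyone contacted came from the insurer's records of cardiovascular patients, so that criterion is covered. For these 43 the article documents no check of the sedentary and no-contraindication criteria listed under Inclusion criteria.

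**3. Do the periods match?** The Abstract counts time from the start of the intervention.

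- QALY follow-up: T0 to T12 = 12 months, of which T5 to T12 = 7 months come after the programme.
- Reimbursement data: 5 + 6 = 11 months. Missing: 1 of 12 months (8.3%), or 1 of the 7 post-programme months (14%).
- If the intervention is taken literally as 20 weeks, that is 20 × 7 / 365.25 × 12 = 4.6 months, and the window is 10.6 months.
- Before inclusion: 12 months. At a constant monthly rate, unscaled totals would give 11/12 = 0.917, an 8.3% lower figure after inclusion with no real change. Converting to a monthly rate removes this, but does not supply the missing month.

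**4. Where does care use enter?** Economic measures places it beside the QALY. The paragraph on programme cost does not list it. EQ-5D supplies the utility weight; hospital stays and consultations are resource use.

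**The case against.** Four points can fairly be made on the other side.

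*The randomised contrast is still there.* The objective names both interventions, the Abstract promises cost-effectiveness for each type of programme, and the general linear model for secondary objectives has experimental condition as its between-subject factor. The 78 may be only an added no-programme reference. This largely stands. A reader might infer that the non-participants replace the PAPA-versus-SPA comparison, and the article does not say so. What remains is that Economic measures specifies only the other comparison, and no section says which one carries the cost-effectiveness conclusion.

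*The 78 need not be wrong.* People could have replied to the insurer and dropped out before phone screening. That stands too. A reader might infer that 78 is impossible, but this follows only if 91 is the total of volunteers, which the article does not state. The figures fail to reconcile; they do not prove an error.

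*The missing month does little harm.* It affects reimbursement data, not programme cost, and supervised sessions have ended by then. It applies to all groups alike, so at equal, constant rates it creates no between-group difference. The phrase about hospitalisations during the protocol might even mean the full period. A reader might infer that all costs lose a month, or that an 8.3% fall will be reported. Neither follows: no before/after comparison of raw totals is specified. The mismatch remains, however. If the window runs from T5, the lost month is the last one, and the primary hypothesis expects the arms to separate over time.

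*No double counting is planned.* Correct. A reader might infer it from the wording on reliability, but no section enters care use in both the QALY and the costs. It becomes a risk only if care use is also costed.

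Nor does the Abstract claim that PAPA is cost-effective; its statement is conditional on effectiveness being shown.

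**Conclusion.** The concern holds in limited form. The QALY comparison as specified is non-randomised and, with the arms pooled, carries no information on PAPA versus SPA. A between-arm economic analysis is possible under the plan but is not named as the economic comparison. The size and direction of the selection bias are unknown.

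The care-use window is 11 months against a 12-month QALY horizon, taking the intervention as 5 months and reading the stated periods literally. The 12-month period before inclusion is not comparable with it unless scaled.

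The 78 are unexplained by at least 43 people, assuming the 56 randomised all came from the 91 screened. Care use is assigned to the wrong side of the cost-effectiveness ratio in the wording.

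The comparator is the most serious part; the window is small but clear. All of this concerns a secondary outcome and leaves the primary IPAQ analysis untouched.

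**What to change.** - State under Economic measures that the economic comparison is PAPA versus SPA as randomised: incremental cost and incremental EQ-5D QALYs over T0 to T12.
- Label the comparison with the 78 as descriptive, and say where they came from, at which stage they left, and whether eligibility was checked. Correct the number if it is wrong.
- Extend the reimbursement extraction to T12 (5 + 7 months), and use monthly rates or equal 12-month periods in any comparison with the year before inclusion.
- Enter hospitalisation and care consumption as costs, and take the QALY from EQ-5D alone.

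The cost is revised wording and one more month in a database request already planned. The downside is that the figure against no programme becomes descriptive. No visit, questionnaire, randomisation or treatment changes.

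### The QALY is defined as a visit value with a life-expectancy purpose and with hospital and care use attached to it, so the effect measure is misdefined and care use is left out of the cost side of the cost-effectiveness comparison

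*Protocol article*

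**What the plan says.** Under Secondary research objectives the article states that "we will evaluate the cost-effectiveness of the two interventions", and it adds the hypothesis that PAPA will be the cheaper programme. The abstract repeats the cost-effectiveness aim.

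The Economic measures section then sets the rules:

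- **Effect.** The QALY "will be calculated at T0, T5 and T12 in order to assess the predicted increase in life expectancy". The instrument is EQ5D: "This assessment allows for the adjustment in life years gained by the quality of life rated on a five-dimension scale".
- **Resource use.** "To improve the reliability of the QALY, we will also include data on the number and duration of hospitalizations during the protocol". Consumption of health care is brought in for the same reason. The source is the reimbursement databases, "for the year preceding inclusion and at 5 months of intervention and 6 months of follow-up".
- **Cost.** "We will also assess program cost by financially assessing the time spent by the various stakeholders, the travel cost for patients", plus materials and rental of the fitness center.

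Under Statistics and data analysis, the only rule for secondary objectives is a general linear model with visit as within-subject factor, condition as between-subject factor, and their interaction. No step accumulates utility over time, and none puts a price on the reimbursement data.

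**The concern.** Three things in the Economic measures section do not fit a cost-effectiveness analysis.

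1. A QALY is utility multiplied by time. A visit yields a utility, and a QALY accrues between visits. The article names a QALY at baseline, where no trial time has passed.
2. Three EQ5D readings within a year, in 56 patients, describe quality-weighted time in that year. They do not estimate life expectancy, and no survival projection is described.
3. Hospital stays and care consumption are quantities of resource use. They have no utility scale, and EQ5D already reflects the health effect of illness, so bringing them into the QALY risks counting the same event twice. Because they are assigned there, they are missing from the listed costs.

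At stake is the cost-effectiveness result, a secondary objective. The effect could be analysed as visit-wise scores instead of accrued QALYs, and cost could be compared without any health care use.

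**Working it through.** The document states no economic figure to reproduce, so the check is of definitions, with arithmetic where it applies.

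**Inputs from the article.** EQ5D visits at months 0, 5 and 12; supervised sessions per week by arm (abstract); the cost items (Economic measures); the model for secondary outcomes (Statistics and data analysis).

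**Accrued QALY.** Write u0, u5 and u12 for the utilities at the three visits. By the trapezoid rule:

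QALY over 12 months = (5/12) × (u0 + u5)/2 + (7/12) × (u5 + u12)/2

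The weights are:
- u0: 2.5/12 = 0.208
- u5: (2.5 + 3.5)/12 = 0.500
- u12: 3.5/12 = 0.292

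They sum to 1, so the maximum is 1.0 QALY. At T0 the elapsed time is zero, so the accrued QALY is 0 for everyone.

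**Visit value against accrued gain.** The utilities below are assumed, and each path is compared with a constant 0.70.

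| Path u0/u5/u12 | 12-month QALY | Gain in QALY | Gain at T12 |
|---|---|---|---|
| 0.70/0.80/0.70 | 0.750 | 0.050 | 0.00 |
| 0.70/0.75/0.80 | 0.754 | 0.054 | 0.10 |
| 0.70/0.85/0.75 | 0.790 | 0.090 | 0.05 |

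The T12 value can miss, overstate or understate the accrued gain.

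**Two arms, again with assumed utilities.**
- PAPA 0.75/0.76/0.80: 0.208 × 0.75 + 0.500 × 0.76 + 0.292 × 0.80 = 0.770
- SPA 0.75/0.80/0.78: 0.208 × 0.75 + 0.500 × 0.80 + 0.292 × 0.78 = 0.784

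The QALY difference (PAPA minus SPA) is 0.500 × (−0.04) + 0.292 × 0.02 = −0.014, while PAPA leads by 0.02 at T12. A model that uses all three visits with equal weight gives (0 − 0.04 + 0.02)/3 = −0.007. That has the right sign but half the size.

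**Cost side.** From the listed items:
- Incremental cost as written = difference in programme cost.
- Incremental cost for cost-effectiveness = difference in programme cost + difference in health care cost.

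The abstract gives SPA 2 × 20 = 40 supervised sessions and PAPA 2 × 10 + 1 × 10 = 30. The programme difference is therefore the value of ten supervised sessions, less what PAPA's telephone calls and materials cost. The health care term is absent from the list. It would reverse the sign of the result if it ran the other way and exceeded the programme difference. The article gives no prices, so neither term can be put in money.

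**The case against.** The best defence is that this is a condensed article with loose wording. Naming T0, T5 and T12 may simply mean the EQ5D visits, which match those of the other secondary measures, and the text does mention life years adjusted for quality. The sentence on cost begins with a word that can be read as adding programme cost to care use already collected. Unit costs and perspective commonly sit in a fuller plan.

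Part of this stands. A missing area-under-the-curve formula would not be a finding by itself, and a fuller document might price the reimbursement data. But the article does more than leave detail out. It states a QALY at baseline, a life-expectancy purpose, and a reason for including hospital data that ties them to the QALY and not to cost.

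Four stronger readings are tempting and are not supported:

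- **That the cost measure is also invalid.** It is labelled programme cost, lists programme items, and answers the stated hypothesis that PAPA costs less.
- **That hospital days are scored into the QALY.** The text says the data will be included and gives no formula, so no arm can be said to earn a particular credit in health units.
- **That the ranking of the arms will reverse.** The reversal above uses assumed utilities and a T12-only comparison, which the plan does not propose. The planned model uses all visits.
- **That the trial promises to show lower medical costs.** The Discussion says this conditionally, about the long term. It is not an endpoint.

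**Conclusion.** The point holds for the effect measure and, for the cost-effectiveness objective only, for the placing of health care use. As written, the QALY is a value per visit that includes a baseline at which it must be zero; its stated purpose cannot be met with 12 months of EQ5D; and resource use is assigned to effect instead of cost. Programme cost remains adequate for the narrow cost hypothesis.

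The weights 0.208, 0.500 and 0.292 follow from the documented visits and the assumption of linear change between them. The example differences (−0.014 QALY, against +0.02 at T12 and −0.007 with equal weights) rest on assumed utilities and show only that the measures are not interchangeable. The health care cost left out cannot be sized from the document. The objective is secondary and the primary analysis is untouched, so this should be corrected but does not threaten the trial's main result.

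**What to change.** In Economic measures:

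1. State that EQ5D utility is measured at T0, T5 and T12.
2. Derive one 12-month QALY per patient as the area under the utility curve (weights 0.208, 0.500, 0.292), and compare PAPA with SPA using T0 utility as covariate.
3. Take hospital stays and care consumption out of the QALY. Value them from the reimbursement data and add them to programme cost for the cost-effectiveness analysis.
4. Keep programme cost alone for the hypothesis that PAPA is the cheaper programme.
5. Delete the life-expectancy purpose.

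No new visits or instruments are needed, since EQ5D and reimbursement data are already planned. The costs are a little more analysis work, a statement of unit costs, and alignment of the reimbursement window with the QALY period: the article gives 5 + 6 = 11 months after inclusion, against a last visit at month 12. The life-expectancy claim is lost.

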**Methods/Design:**

Cardiovascular patients (*N* = 56) will be individually randomized into two groups. Two supervised physical activity (SPA) sessions per week will be offered to the first group for 20 weeks. Progressively autonomous physical activity (PAPA) will be offered to the second group as follows: 10 weeks of the same supervised program as the SPA group followed by 10 more weeks in which one supervised session will be replaced by a strategy to build and sustain the habit of autonomous practice of physical activity. The primary outcome is the amount of physical activity measured by the International Physical Activity Questionnaire (IPAQ; Craig et al., Med Sci Sport Exercises 35(8):1381–95, 2003). To compensate for the limited capacity to recruit subjects, multiple IPAQ measurements will be made (at T0, T5, T7, T9 and T12 months after the start of the intervention) and analyzed using the mixed model approach. We will also assess changes in physical and physiological indicators, automaticity of the physical activity behavior, motivation and quality of life. Last, we will assess the cost-effectiveness for each type of program.

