## Discussion

Cardiovascular patients are generally willing to take part in CR, but unfortunately they do not systematically have the opportunity to do so (80 % of our sample). The PAPA intervention is designed to complement secondary prevention programs or replace them for those who cannot easily participate. The intervention aim is to provide cardiovascular patients with an opportunity to progressively learn, adopt and maintain PA behaviors.

The data from this study will be used to assess the impact of the *As du Coeur* intervention just after the end of the intervention (T5). We do not expect significant differences between the PAPA group and the fully supervised group at this point. Indeed, the fully supervised group will have more supervised sessions that the autonomous group (two per week versus one per week in the second half of the intervention). Based on the linear trend in the PA measures made in the months following the end of the intervention, we expect to find a decline in PA (negative linear slope of the time effect) post-intervention only for the SPA group. We expect that patients of the PAPA group will either maintain the same level (null slope) or even increase their PA (positive slope) in the months following the end of the intervention. Despite our low sample size due to a limited recruitment capacity, it is important to recall that this hypothesis can still be adequately tested with reasonable power using a mixed model approach, as simulation studies of the power in mixed model have shown that it typically increases with repeated measurements [23]. However, we will carry out exploratory analyses to test whether the PAPA intervention also leads to greater automaticity and motivation for PA, higher quality of life and better physical condition compared with the SPA intervention. Another limitation of the study can be the used of the sport motivation scale to assess participant’s motivation in the context of PA as motivation for sport and physical activity can differ.

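### Health-care-use data are planned to month 11 (5 + 6 months), one month short of the T12 end point of the QALY they support

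*Protocol article*

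**What the plan says.** All of the following comes from the Protocol article.

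- **QALY times (Economic measures):** "The quality-adjusted life-year (QALY) will be calculated at T0, T5 and T12".
- **Purpose of the claims data (same section):** "To improve the reliability of the QALY, we will also include data on the number and duration of hospitalizations during the protocol", together with health-care consumption.
- **Claims window (same section):** the information comes from "reimbursement databases for the year preceding inclusion and at 5 months of intervention and 6 months of follow-up".
- **Time origin (Abstract, Methods/Design):** the IPAQ is measured "at T0, T5, T7, T9 and T12 months after the start of the intervention", which fixes what the T labels mean.
- **End of intervention (Discussion):** placed at T5. The Intervention section also gives the supervised programme a length of 5 months.
- **Status of the analysis (Secondary research objectives):** "Last, we will evaluate the cost-effectiveness of the two interventions".

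No other section mentions a 6-month follow-up or extends the claims extraction to month 12.

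**The concern.** Resource use and health effects in a cost-effectiveness analysis should cover the same period. Here the QALY runs to month 12, while the health-care-use data meant to strengthen it stop at month 11.

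The section also disagrees with itself. It promises hospitalisations throughout the protocol, and an admission in month 12 is within the protocol but outside the stated window.

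What is at stake is the last month of health-care use. The primary objective expects no difference between arms at the end of the intervention and a difference that appears later. If health-care use followed that pattern, the omitted month would be among the most informative. This is an assumption: the article makes no such claim about health-care use.

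The look-back before inclusion is a full year, so the on-study window is also one month shorter than the period it might be compared with.

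**Working it through.** The check is calendar arithmetic.

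**Inputs**
- QALY end point: 12 months (Economic measures).
- T labels: months from the start of the intervention (Abstract).
- End of intervention: month 5 (Discussion; Intervention).
- Claims window: 12 months before inclusion, then 5 months of intervention and 6 months of follow-up (Economic measures).
- Randomised: 56, with 28 per arm (Sample size).

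**Step 1. The window as stated.** 5 + 6 = 11 months.

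**Step 2. The follow-up implied by the visit schedule.** 12 − 5 = 7 months.

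**Step 3. The gap.** 12 − 11 = 1 month, or equivalently 7 − 6 = 1 month.
- Share of on-study time: 1/12 = 8.3%.
- Share of follow-up: 1/7 = 14.3%.
- Person-months, all randomised: 56 × 1 = 56 of 56 × 12 = 672.
- Person-months, per arm: 28 of 28 × 12 = 336.

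**Step 4. Do other readings close the gap?**

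| Reading | Window ends at | Gap to T12 |
|---|---|---|
| Periods of 5 and 6 months | 11 months | 1 month |
| Dates on which the databases are queried | T5 and T11 | 1 month |
| Intervention taken as exactly 20 weeks (Abstract): 20 × 7 / 30.4375 = 4.6 months | 4.6 + 6 = 10.6 months | 1.4 months |

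None reaches T12 as long as follow-up starts when the intervention ends.

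**Step 5. Before/after comparison, if one is made.** Assume constant monthly use.
- Raw totals: 11/12 − 1 = −8.3%, an apparent fall where there is none.
- Use per month: (11/11)/(12/12) − 1 = 0%.

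The article does not say which form would be used, or that this comparison is planned.

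**Step 6. Between-arm difference.** No rates or costs of health-care use are given, so the effect of the lost month on this difference cannot be computed.

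**The case against.** The strongest reply is that this is a one-word slip in a condensed article. The main end points run to T12, the section speaks of hospitalisations over the whole protocol, and exact extraction dates usually sit in a fuller document. The 6 may simply be a mistake for 7. That may well be so, but the article states a window, and the window is wrong for its purpose. This is not a detail left out. Anyone who extracts data from this sentence will stop a month early.

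It can also be said that little changes. The QALY itself rests on the EQ5D at T0, T5 and T12 and is not truncated. The claims data are supplementary, both arms lose the same month, and the 8.3% in step 5 arises only if unscaled totals are compared. All of this stands, and it is why the point is minor.

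Finally, Economic measures also names a comparison group of 78 volunteers who did not take part, and the person-month counts above leave them out. That is correct. The article does not say whether their data come from the same databases. If they do, one further month means 56 + 78 = 134 person-months rather than 56. The error and its correction stay the same.

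**Conclusion.** The concern holds, as a minor point. The stated claims window ends at month 11 and the QALY at month 12, so one month of health-care use is missing from a named secondary objective: 8.3% of on-study time and 14.3% of follow-up.

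This rests on two things that the article itself supplies: T12 is counted from the start of the intervention, and follow-up begins at T5. It also assumes that the window will be applied as written.

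The lost month is the same in both randomised arms, so neither is favoured by the length of the window. The size of any effect on the cost-effectiveness result is unknown. Programme cost is assessed separately, and that assessment, the primary IPAQ analysis and the sample size are untouched.

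**What to change.** In Economic measures, replace 6 months of follow-up with 7. State that reimbursement data will be extracted from each participant's start date through T12, and that health-care use and QALYs will be reported over the same 12-month horizon in both arms. If the 78 non-participants are drawn from the same databases, give them a window of the same length.

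If 6 months is deliberate, for example because of late claims, give the reason and express use per month, so that the 11-month and 12-month periods can be compared.

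The cost is one more month of routine insurer data per participant, 56 person-months for the randomised sample, with no new visits or measures. Extraction may have to wait a little after T12 for late claims; the article does not give the claims delay.
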